## Abstract

**Background:**

Integrating artificial intelligence (AI) with mobile health is revolutionizing chronic disease management. Non-specific lower back pain (NSLBP), a leading worldwide disabling condition, negatively impairs patient quality of life and psychological status. Standard treatments, mostly pharmacological and physiotherapies, do not offer long-term support for self-management. Consequently, we developed the AI-Health Education Accurately Linking System (AI-HEALS) to investigate its application in improving self-management, alleviating pain, and enhancing overall life quality for NSLBP patients.

**Methods:**

This study utilizes a randomized controlled trial (RCT) to evaluate the effectiveness of a three-month AI-HEALS intervention in improving self-management among patients with NSLBP. Participants are randomly assigned to either a control group receiving standard care or an intervention group receiving standard care supplemented by the AI-HEALS program. The intervention features an AI-powered, voice-activated interactive Q&A system, along with physiological monitoring, regular reminders, and tailored educational content. These services are primarily delivered via a WeChat official account titled “NSLBP Health Management Expert.” The AI-HEALS system builds its knowledge base based on NSLBP treatment guidelines to ensure the accuracy and reliability of the information provided. The primary outcome measure is pain intensity, while secondary outcomes assess self-management behaviors, psychological well-being, and physiological parameters.

**Discussion:**

AI-HEALS program combines AI with mobile health to provide an organized platform for efficient home care of NSLBP, alleviating pain, enhancing quality of life, and lessening dependency upon conventional medical resources. Results from this study will establish AI-HEALS’ effectiveness in managing chronic diseases and provide a science basis for subsequent health intervention.

**Clinical trial registration:**

Identifier, CHICTR2400090707.

## Introduction

1

Non-specific lower back pain (NSLBP) refers to a condition caused by acute or chronic damage to the muscles, fascia, and other soft tissues of the lower back due to trauma, lumbar disk herniation, and other factors (1, 2). It is a common global health issue that significantly impacts people’s quality of life and work efficiency (1, 3). The prevalence of NSLBP globally is approximately 7.6%, with a rapid increase observed over the past two decades (4). Compared to spinal injuries or other diseases with clear physiological etiologies, the treatment and prognosis of NSLBP face greater challenges due to its often unclear causes (1, 2). The condition not only leads to long-term and recurrent pain in patients but may also cause functional impairments and activity limitations, increasing the risk of anxiety and depression (5, 6). These symptoms significantly reduce the quality of life, including sleep disturbances and reduced social activities (3, 7, 8). The persistent nature of chronic pain not only exacerbates the psychological and economic burden on family members but also affects emotional communication and social functions within the family (9, 10). Moreover, patients’ increased dependency on external support necessitates additional care and support from family members, potentially leading to an imbalance in family dynamics (9, 10).

From a social and economic perspective, NSLBP is one of the leading causes of work absenteeism and decreased work capacity (11–13). Studies indicate that NSLBP, along with widespread lower back pain, is the leading cause of work disability among the working-age population (11–13). This condition not only imposes a significant economic burden on individuals and families but also exerts substantial pressure on the socioeconomic system, resulting in extensive consumption of medical resources and notable productivity losses (11–13). According to data from the Global Burden of Disease (GBD) Study, low back pain ranked as the sixth leading cause of disability-adjusted life years (DALYs) worldwide in 2019, accounting for approximately 63.7 million DALYs—an increase of nearly 47% since 1990 (14). Furthermore, the 2021 GBD Study confirmed that low back pain remains among the top 10 causes of DALYs globally, underscoring its persistent and considerable public health impact (15).

Current conventional interventions for NSLBP encompass a variety of approaches, including pharmacotherapy, physical therapy, psychological interventions, and lifestyle modifications (3, 7, 16). Pharmacological treatments primarily rely on non-steroidal anti-inflammatory drugs and muscle relaxants, which can effectively alleviate pain but may cause gastrointestinal issues and dependency when used long-term (17, 18). Physical therapies, such as massage, heat therapy, and acupuncture, improve local blood circulation and relieve muscle tension and pain, yet they typically require patients to regularly visit healthcare facilities, increasing both time and financial burdens (19–21). Psychological interventions, such as cognitive-behavioral therapy, aim to alter patients’ perceptions and coping strategies regarding pain, helping to mitigate the psychological burdens associated with chronic pain (22, 23). However, such psychological interventions require the involvement of professional psychologists, making them difficult to widely implement in resource-limited areas (22, 23). As for lifestyle adjustments, such as increasing moderate exercise and improving sleep quality, while these have long-term benefits for symptom and pain management, they also depend heavily on the patient’s self-management capabilities and sustained motivation, which can result in significant variability in effectiveness (24–26).

On the whole, there are some limitations with existing treatments for NSLBP. To begin with, some of these treatments necessitate patients’ multiple visits to health facilities, which can be inconvenient for patients residing in rural areas or with tight workloads. Secondly, these traditional treatments such as pharmacotherapy and physical therapy carry adverse effects and may not be applicable to all patients. Thirdly, the unequal availability of resources for psychological intervention restricts these types of intervention from being used over wider areas.

Currently, over 75% of the global population has access to mobile phones with internet capabilities, while more than 57% of households have an internet connection (27, 28). In Europe, these figures reach as high as 99 and 86%, respectively (27, 28). These statistics highlight the indispensable role of smartphones in daily life and their potential significance in health management and lifestyle adjustments, particularly in facilitating communication between healthcare professionals and patients. Traditionally, mobile health interventions primarily relied on voice services or text-based Short Message Service (29–31). However, with the increasing availability and usability of applications, there has been a significant rise in the number of smartphone apps specifically designed to alter health behaviors (29, 32). These apps encompass a wide range of areas, including pain management, chronic disease management, weight control, and the management of smoking and other addictive substances (29–32). Taking the study by Piette et al. as an example, they designed an intervention combining artificial intelligence with an interactive voice response system for 278 veterans suffering from chronic back pain over a 10-week period (33). The results indicated that this intervention was as effective as cognitive behavioral therapy for chronic pain (CBT-CP) delivered by therapists over the phone, but required significantly less therapist time. Such AI-assisted CBT-CP interventions could enable the same number of therapists to effectively serve a larger number of patients. Economically, the study by Fatoye also yielded positive results. Implementing remote multidisciplinary management for NSLBP patients, they found that remote rehabilitation could save approximately 16,000 Naira (about 44.3 USD) per patient (34). These observations highlight the cost savings from telemedical treatment using advanced communication media and their potential for extensive use.

In this context, the deployment of the Artificial Intelligence-Health Education Accurately Linking System (AI-HEALS) via WeChat, China’s largest social media site, assumes special relevance. It employs cheap, ubiquitous mobile communication technology so that patients are able to receive support and management from their own homes. AI-HEALS intervention content relies on the HAPA-MTM theoretical model, addressing not only physiological symptom management but also highlighting psychological health and changes in behavior, providing an integrated and extended approach to disease management (35–37). Highlight of the system includes AI-based knowledge Q&A from a tailored knowledge base, tracking of physiological markers and behaviors, different reminder services, and message dissemination tailored to each individual. Such an innovative intervention model is well-suited for contemporary society’s needs and can potentially provide efficient support and management for many patients with NSLBP.

In summary, this study is intended to assess the efficacy of AI-HEALS intervention program among patients with NSLBP on their self-management outcome by conducting a randomized controlled trial (RCT) in the following areas:

Evaluate the efficacy of the three-month multifaceted AI-HEALS intervention in enhancing physiological indicators among the NSLBP population;Assess the efficacy of the three-month integrated AI-HEALS intervention for improving psychological indicators in the NSLBP population;Evaluate the efficacy of the three-month overall AI-HEALS intervention in enhancing behaviors of self-management among NSLBP individuals.

## Materials and methods

2

### Design

2.1

This is a mixed-method study utilizing a randomized, single-blind, parallel-group controlled clinical trial conducted at a public comprehensive hospital in Chengdu, Sichuan, China. The study involves individuals diagnosed with NSLBP and is a single-center investigation. The study flowchart is shown in Figure 1.

**Figure 1 fig1:**
[figure not shown]
Flow chart of patient recruitment and study implementation.

### Randomization and blinding

2.2

Randomization in this study is based on a computer-generated random number sequence. Participants will be assigned to intervention and standard care groups at a 1:1 ratio. Randomization will be carried out before patient enrollment so that each patient is assigned to the study’s respective group according to a pre-determined sequence, ensuring randomness and equity. Upon entry, every patient will be given an individual code that corresponds to the random number sequence, with continuous and smooth enrollment. Once randomized, patients will be transferred to an appropriate ward according to their assignment. Intervention group patients, for instance, will be admitted to Ward A, while control patients will be admitted to Ward B to avoid any possible cross-contamination between intervention strategies.

For the purpose of maintaining the confidentiality of the allocation sequence, an impartial team member will conduct the randomization process, who does not engage in participant recruitment nor gets involved in the allocation. This will prevent divulgence of the sequence in the course of the study. The team member will then communicate the allocation outcome to the intervention team, ensuring that neither the participant recruitment team nor the intervention team gains any prior knowledge of the allocation.

Lastly, due to the novelty of AI-HEALS intervention in this trial, total participant and therapist blinding is not possible. This limitation is bound to induce some biases, including performance bias due to participant unawareness of treatment assignment and detection bias due to therapists’ knowledge of the intervention adopted. To reduce these biases, we will implement a series of strategies to mitigate their effects on the study. First, confidentiality of all intervention and control group participants’ identities will be maintained until study completion. Second, a separate team member not involved in participant registration or intervention delivery will be responsible for conducting random allocation. An independent staff member will personally inform the intervention team of the allocation results, ensuring that the enrollment team remains blinded to group assignments. Third, intervention patients will be hospitalized in Ward A, with control patients in ward B, to avoid cross-contamination between study groups. Lastly, to further minimize bias factors, study data will be gathered by study assistants who remain blind to allocation. In the analysis process, data analysts will also remain unaware of group assignments. During the study, all data will be coded and stored in a password-protected, encrypted electronic database with access restricted to authorized study personnel only. Any physical documents will be kept in locked cabinets within secure research facilities. These measures ensure confidentiality and comply with institutional ethics requirements while preserving the integrity of the blinding process.

### Study sample

2.3

All patients diagnosed with NSLBP are eligible to participate. Additionally, participants must meet the following criteria:

#### Inclusion criteria

2.3.1

According to the doctor’s clinical diagnosis, the participant meets the diagnostic criteria for nonspecific low back pain, which means there is no clear organic cause for the low back pain (1, 2).The duration of the low back pain exceeds 6 weeks, classifying it as chronic low back pain (3, 29).The participant owns a smartphone, is proficient in its use, and is willing to receive and participate in the intervention program through the WeChat platform.The participant is aged 18 or older.The participant is willing and able to sign an informed consent form and participate in the entire study period.

#### Exclusion criteria

2.3.2

Lack of basic reading and writing skills, unable to receive and understand health information via WeChat;Presence of severe cardiovascular, renal, or other major organ dysfunctions;Abnormal cognitive abilities or psychiatric conditions that preclude cooperation;Pregnancy or currently breastfeeding;Known severe allergies to any materials, devices, or components used in the intervention;Active substance abuse or dependence that may interfere with participation;Severe frailty, inability to independently use a smartphone, or inability to complete study follow-up;Currently participating in other similar research studies;Unwilling to cooperate or Other reasons that make participation in the trial inappropriate.

#### Withdrawal criteria

2.3.3

Participants who voluntarily request to withdraw from the study for personal reasons, such as scheduling conflicts or changes in interest;Occurrence of severe adverse events during the study, such as serious physical illnesses or acute events (e.g., heart attack, severe infection) that require interruption of the intervention;Changes in medical condition or other medical advice that necessitate altering the original treatment plan, potentially conflicting with the study intervention.

### Sample size

2.4

G-Power 3.1.9.4 was used to calculate the sample size. The effect size was 0.68 (33), efficacy was 0.80, alpha was set at 0.05, and one-tailed tests were performed based on previous studies. The calculated required sample size was determined to be at least 58 (29 participants per group). We estimated an attrition rate of 20%, so a total sample of at least 74 participants (37 per group) was required.

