
### Statistical analysis

2.13

In this study, quantitative data will be collected through questionnaires and stored in Microsoft Excel format. Data analysis will follow the intention-to-treat principle. For continuous variables, results will be presented as mean ± standard deviation or as median with interquartile range (P25, P75), depending on the normality of the distribution, which will be assessed using the Kolmogorov–Smirnov test. Appropriate statistical methods, such as Student’s t-test, one-way ANOVA, or non-parametric tests, will be used for group comparisons. Categorical variables will be expressed as counts and percentages (n, %) and analyzed using the chi-square test.

To explore the relationships between behavioral patterns and mobile health application use, linear regression, logistic regression, and structural equation modeling will be applied to cross-sectional data. For longitudinal analyses, generalized linear mixed models will be used to assess the impact of AI-HEALS interventions on behavior change and NSLBP management over time. Subgroup analyses will be conducted based on patients’ levels of family communication and eHealth literacy to refine and contextualize the findings.

Missing data will be addressed using multiple imputation by chained equations (MICE), with 50 iterations to ensure convergence. Predictive mean matching (PMM) with five nearest neighbors will be employed, generating 20 imputed datasets. All statistical tests will be two-sided, with a significance level set at 0.05. Data will be analyzed using IBM SPSS Statistics 24.0 (SPSS Inc., Chicago, IL, United States), Stata 14.0 (StataCorp, College Station, TX, United States), and Mplus 7.4 (Muthén & Muthén, Los Angeles, CA, United States).

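### Section 2.4 sizes the trial for a one-tailed test, but Section 2.13 makes all tests two-sided; at the required 29 completers per arm, two-sided power is about 72%, not 80%

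*Protocol article*

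**What the plan says.** Section 2.4 (Sample size) gives the inputs in one sentence: "The effect size was 0.68 (33), efficacy was 0.80, alpha was set at 0.05, and one-tailed tests were performed based on previous studies". The word efficacy there evidently means power. The result follows: "The calculated required sample size was determined to be at least 58 (29 participants per group"). An assumed 20% attrition raises this to 74 enrolled, 37 per group. Section 2.2 fixes 1:1 allocation.

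Section 2.13 (Statistical analysis) states: "All statistical tests will be two-sided, with a significance level set at 0.05". It makes no exception for pain intensity, the primary outcome. It lists Student's t-test among the methods for comparing groups and names generalized linear mixed models for longitudinal analyses.

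Section 2.4 takes the effect size from reference 33. The Introduction describes that study as an AI and interactive voice response programme for veterans with chronic back pain, and reports: "The results indicated that this intervention was as effective as cognitive behavioral therapy for chronic pain (CBT-CP) delivered by therapists over the phone". The comparator in the present trial is standard care (Section 2.7.1).

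**The concern.** The sample size and the analysis describe two different tests of the same hypothesis. At the same nominal 0.05, a two-sided test has a higher critical value than a one-tailed test, so the same number of patients gives less power. Nothing in the article reconciles the two sections.

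What is at stake is how a null result would be read. Someone relying on Section 2.4 would believe that a true difference of 0.68 had a 20% chance of being missed, when at the planned number of completers that chance is larger. Type I error is not affected, because the two-sided analysis is valid in itself.

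A second, smaller matter is the source of 0.68. The one result that the article reports from reference 33 is similarity between two active treatments. That does not by itself support 0.68 as a difference from standard care.

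**Working it through.** **Inputs.** Standardised difference d = 0.68, power 0.80, alpha 0.05, one-tailed, 29 per group, 20% attrition (Section 2.4); 1:1 allocation (Section 2.2); two-sided alpha 0.05 (Section 2.13). Section 2.4 names no test. I assume an unadjusted two-sample t-test.

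**Formula.** With n per group, the degrees of freedom are 2n − 2 and the noncentrality parameter is d × √(n/2). Power is the probability that a noncentral t variable exceeds the critical value. The two-sided case adds the negligible probability in the opposite tail.

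**Reproducing the plan's figure (one-tailed).**
- n = 28: noncentrality 0.68 × √14 = 2.544, critical value 1.674, power 0.807. This is the smallest n that reaches 0.80, giving 56 in total.
- n = 29: noncentrality 0.68 × √14.5 = 2.589, critical value 1.673, power 0.819.

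The stated 58 is within two patients of the one-tailed t-test minimum. The attrition step also reproduces: 29/0.8 = 36.25, rounded up to 37 per group, or 74. The fault therefore lies in the sidedness and not in the rest of the arithmetic.

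**Applying the test in Section 2.13 (two-sided 0.05).**

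| Completers per arm | Noncentrality | Critical value | Two-sided power |
|---|---|---|---|
| 29 | 2.589 | 2.003 | 0.721 |
| 34 | 2.804 | 1.997 | 0.789 |
| 35 | 2.845 | 1.996 | 0.801 |
| 37 (no attrition) | 2.925 | 1.994 | 0.823 |

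- Type II error at 29 per arm: 1 − 0.721 = 0.279.
- Two-sided 80% power: 35 completers per arm, 70 in total. With 20% attrition, 35/0.8 = 43.75, so 44 per arm and 88 enrolled, which is 14 more than the planned 74.
- Difference detectable with 80% two-sided power at 29 per arm: d = 0.749, about 0.75.

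**The case against.** **Enrolment is 74, not 58.** If all 37 per arm gave outcome data, two-sided power would be 82%. This stands as a condition on the finding: the shortfall appears only through dropout. It does not remove the finding, because Section 2.4 itself expects 20% loss and sets 29 per arm as the requirement. Multiple imputation, planned in Section 2.13, does not in general restore information lost to dropout.

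**The t-test may not be the main analysis.** Section 2.13 plans mixed models for longitudinal questions, and using the baseline value could raise power. As an illustration, assume 0.68 is on the raw-score standard deviation and the correlation r between baseline and outcome is 0.3 or 0.5. Dividing d by √(1 − r²) gives power of 0.76 or 0.84 at 29 per arm. This also stands, so the 72% must be labelled as belonging to an unadjusted t-test. Section 2.4, however, states no correlation and takes no credit for one, so the stated 80% cannot be defended that way as written.

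**One-tailed may have been deliberate.** Then Section 2.13 would be the passage in error. One of the two has to change in either case.

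**The source of 0.68.** A reader might infer that 0.68 cannot come from reference 33, or that the citation should be dropped. The documents do not support that. Section 2.4 gives no comparator, outcome or time point for the figure; the Introduction summarises the study's result in one sentence; and the source itself is not at hand. The figure could, for example, be a within-group change.

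**Conclusion.** The contradiction is explicit, and the stated 80% power does not belong to the planned two-sided test. At d = 0.68 and 29 completers per arm, an unadjusted two-sample t-test has about 72% power, roughly 8 percentage points below the stated figure and 10 below the 82% that the same test has one-tailed.

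This rests on three conditions: 0.68 is the true standardised difference, attrition is the planned 20% with enrolment at the stated minimum, and no precision is gained from baseline or repeated measurements. A reader might infer that the trial is underpowered under any analysis and any retention; the figures for full retention and for baseline adjustment show that this does not follow. What does follow is that the power statement is wrong as written, and that 0.68 is an assumption for which the protocol gives no clear basis as an effect against standard care.

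**What to change.** Keep the two-sided tests and replace the power statement in Section 2.4 with wording such as: 58 completers (29 per group) give about 72% power for an unadjusted two-sample t-test at two-sided alpha 0.05 and d = 0.68; the effect detectable with 80% power is d = 0.75.

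In the same place, label 0.68 as an assumption, since the Introduction's description of reference 33 does not by itself support it as an effect against standard care.

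The cost is a change of wording and a less favourable power figure. No extra patients are needed for this correction. Restoring 80% two-sided power under the unadjusted t-test would instead mean enrolling 88. The trial began in April 2025 and is expected to end in December 2026, so the statement should be corrected before results are known.

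### The trial is sized for a one-tailed test at 0.05 but will be tested two-sided at 0.05, so the stated 80% power is about 72%

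*Protocol article*

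**What the plan says.** Section 2.4 of the protocol article (Sample size) gives these inputs: "The effect size was 0.68 (33), efficacy was 0.80" (the word used for power is evidently a mistranslation), and "alpha was set at 0.05, and one-tailed tests were performed based on previous studies". The result is a minimum of 58 patients, 29 per group. The section continues: "We estimated an attrition rate of 20%, so a total sample of at least 74 participants (37 per group) was required".

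Section 2.13 (Statistical analysis) sets the testing rule: "All statistical tests will be two-sided, with a significance level set at 0.05". For the comparison itself it says: "Appropriate statistical methods, such as Student’s t-test, one-way ANOVA, or non-parametric tests, will be used for group comparisons".

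Section 2.2 fixes the allocation: "Participants will be assigned to intervention and standard care groups at a 1:1 ratio". Nothing in the article reconciles the one-tailed sizing with the two-sided rule or exempts the primary comparison, pain intensity, from that rule.

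**The concern.** A one-tailed test at 0.05 puts the whole 5% in the favourable direction. A two-sided test at 0.05 allows 2.5% there, so it needs a larger observed difference to reach significance. A sample that gives 80% power for the first gives less for the second.

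Two things are at stake:

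- **The stated power.** If the trial is null, readers will judge that result against a sensitivity of 80% that the design does not have.
- **The threshold for success.** A one-tailed p-value of 0.04 in the favourable direction is 0.08 two-sided. It succeeds on the basis used in section 2.4 and fails under section 2.13. That should be settled before anyone sees results by group.

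**Working it through.** **Inputs**

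| Input | Value | Source |
|---|---|---|
| Standardised difference d | 0.68 | Section 2.4 |
| Power | 0.80 | Section 2.4 |
| Alpha, sizing | 0.05, one-tailed | Section 2.4 |
| Alpha, analysis | 0.05, two-sided | Section 2.13 |
| Allocation | 1:1 | Section 2.2 |
| Evaluable / randomised per group | 29 / 37 | Section 2.4 |
| Attrition | 20% | Section 2.4 |

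**Assumption.** Section 2.4 does not name the test chosen in the sample size software. I use the two-sample t-test, and show the rank test (Wilcoxon-Mann-Whitney) as the alternative, because section 2.13 allows either.

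**Formula.** With n per group, df = 2n − 2 and noncentrality δ = d × √(n/2). Power is the probability that a noncentral t variable with these parameters exceeds the critical value: the 95th percentile of t for the one-tailed test, the 97.5th for the two-sided test. (The opposite tail adds a negligible amount.) For the rank test, n is multiplied by 3/π ≈ 0.955, its efficiency relative to the t-test for normal data.

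**Step 1: reproduce the plan's figure.** One-tailed 0.05:

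- t-test: 27 per group gives 0.794 and 28 gives 0.807, so 28 suffice. At 29, power is 0.819.
- Rank test: 28 per group gives 0.791 and 29 gives 0.803, so 29 are needed. This is exactly the stated figure.
- Attrition: 29 / 0.8 = 36.25, rounded up to 37 per group, 74 in total. This matches.

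The plan's figure is therefore a one-tailed figure. The two-sided minimum is 35 by t-test, so 29 cannot have come from a two-sided calculation.

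**Step 2: apply the two-sided test to the planned 29.**

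δ = 0.68 × √(29/2) = 2.589, df = 56. The critical value rises from 1.673 (one-tailed) to 2.003 (two-sided).

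| Test, n = 29 per group | One-tailed 0.05 | Two-sided 0.05 |
|---|---|---|
| t-test | 0.819 | 0.721 |
| Rank test | 0.803 | 0.700 |

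The type II error is 1 − 0.721 = 0.279 by t-test, or 1 − 0.700 = 0.300 by rank test, against the stated 0.20.

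**Step 3: what 80% two-sided power would need at d = 0.68.**

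| | t-test | Rank test |
|---|---|---|
| Evaluable per group | 35 (0.801; 34 gives 0.789) | 37 (0.805; 36 gives 0.794) |
| Randomised per group at 20% attrition | 35 / 0.8 = 43.75 → 44 | 37 / 0.8 = 46.25 → 47 |
| Randomised in total | 88 | 94 |

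**Step 4: what the planned size can deliver.**

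- Difference detectable with 80% two-sided power at 29 per group: 0.75 by t-test (0.749), 0.77 by rank test (0.767).
- If all 37 randomised per group were evaluable, two-sided power would be 0.823 by t-test and 0.805 by rank test.
- By t-test, 80% is kept only if 35 of 37 remain, a loss of 2 / 37 = 5.4% per group. By rank test it is kept only with no loss at all. The plan expects 20%.

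**The case against.** Nobody can fairly deny the conflict between the two sections. The case on the other side concerns how firmly the 72% can be stated and how much it matters.

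- **Test family.** The rank test reproduces 29 exactly and the t-test gives 28, so the authors may have sized for a rank test, in which case the figure is 70%. This stands as a point of precision: the corrected text should name its test. It makes the shortfall slightly larger.
- **The planned analysis is richer than one comparison of completers.** Section 2.10.1 places the primary outcome at several time points, and section 2.13 plans intention-to-treat analysis, mixed models and multiple imputation, so patients with partial follow-up contribute. This stands as a limit on what 72% means. It does not rescue the stated 80%: section 2.4 takes no credit for repeated measures or imputation, and the article gives no correlation from which a gain could be computed.
- **The numbers are minimums.** Enrolling more, or losing fewer, would raise power. That is true, but the plan's own 20% attrition is what brings 37 down to 29.
- **Neither section claims precedence.** Strictly, the documents show only that the sections disagree. Reading section 2.13 as governing is a judgement, though a strong one: it covers every test without exception, while the only reason given for one tail is earlier studies.
- **Validity is not threatened.** The two-sided test is the stricter one, effect estimates are unaffected, and a null result can still be read from its confidence interval. All this is correct. The fault is a misstated design property and an unsettled success threshold, not a biased result.

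**Conclusion.** The concern holds. The trial was sized for a one-tailed 5% test and will be analysed with two-sided 5% tests. On the plan's own inputs (d = 0.68, 1:1 allocation, 29 evaluable per group after 20% attrition), two-sided power is 72% by t-test or 70% by rank test, not 80%. The planned size has 80% two-sided power for a difference of about 0.75 by t-test (0.77 by rank test).

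These figures assume a single unadjusted two-group comparison at one time point, the minimum enrolment, the full planned attrition and, for the rank test, normal data. They do not describe the power of the longitudinal mixed model, which the article gives no inputs to compute.

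**What to change.** Keep two-sided testing as in section 2.13 and correct section 2.4 to match. Remove the one-tailed basis and replace the power statement with one that names the test, for example:

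> With 37 patients randomised and 29 evaluable per group, a two-sided 5% two-sample t-test has 72% power for a standardised difference of 0.68 and 80% power for 0.75. For a rank test, the power at 0.68 is about 70%.

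Do not resolve the conflict by making the primary test one-sided at 0.05. That would double the false-positive rate allowed in the favourable direction, from 2.5% to 5%.

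If the sponsor wants to keep 80% power at 0.68, the matching t-test figures are 35 evaluable and 44 randomised per group (88 in total). This is optional; restating the power is enough.

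The cost is a short correction to section 2.4 and a less favourable power figure. No extra patients are needed. Section 2.13 is unchanged. The article gives April 2025 as the start and December 2026 as the expected end, so the correction should be made and dated before any results by group are seen.
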